### Analysis plan

A statistical analysis plan will be written and agreed by the Trial Steering Committee and Data Monitoring Committee before any analysis is undertaken. All statistical analyses will be carried out using the latest version of R software [46]. All analyses will be done in accordance with intention-to-treat principle where all children and parent outcomes are analysed as randomised. In accordance with CONSORT statement for non-pharmacological interventions, we will report all participant flow. Data will be summarised by trial arm. N, Mean ± SD, (or median ± IQR if data are skewed), Minimum and Maximum will summarise continuous variables, whereas number and percentages will be used to summarise categorical variables.

The analysis of the primary outcome at 24 weeks will use generalised estimating equations with binomial distribution and logit link. Exchangeable working correlation will be used to account for the clustering of children by parent groups. The continuous secondary outcomes will first be analysed at 24 weeks using a difference-in-difference model based on linear mixed effect model accounting for paired data (at baseline and at 24 weeks) per child and clustering of children by parent groups. The same model will be applied to the data at week 52, which will be analysed as longitudinal data incorporating data at baseline and 24 weeks. All binary or categorical secondary outcomes will be analysed using generalised estimating equations. We will also perform subgroup analysis and safety analysis, sensitivity analysis for missing data and assess the impact of the COVID-19 pandemic on primary and secondary outcomes.

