**Methods:**

The study is a clinical and cost-effectiveness, multi-site randomised controlled trial of the Managing Repetitive Behaviours (MRB) parent group intervention versus a psychoeducation parent group Learning About Autism (LAA) (*n* = 250; 125 intervention/125 psychoeducation; ~ 83/site) for parents of young children aged 3–9 years 11 months with a diagnosis of autism.

All analyses will be done under intention-to-treat principle. The primary outcome at 24 weeks will use generalised estimating equation (GEE) to compare proportion of children with improved RRB between the MRB group and the LAA group. The GEE model will account for the clustering of children by parent groups using exchangeable working correlation. All secondary outcomes will be analysed in a similar way using appropriate distribution and link function.

The economic evaluation will be conducted from the perspective of both NHS costs and family access to local community services. A ‘within trial’ cost-effectiveness analysis with results reported as the incremental cost per additional child achieving at least the target improvement in CGI-I scale at 24 weeks.

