## Methods and design

### Study design

This study is a UK three-site, two-group RCT. After consent families will be randomised at each site to receive either the 8-week MRB parent group intervention or the 8-week Learning About Autism (LAA) parent group equivalent to best current practice and will act as an attentional control for time and attention. Assessments are administered on entry (baseline) to the trial, at the end of the eight parent group sessions (10 weeks), at 24 weeks primary endpoint and at the 52 weeks follow-up.

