### Study aims

The aim of this study is to evaluate the clinical and cost-effectiveness of the Managing Repetitive Behaviours (MRB) parent group intervention for young children with autism compared with a parent autism psychoeducation group, at 10, 24 and 52 weeks follow-up.

The clinical effectiveness of this intervention will be assessed by measuring whether children show an overall improvement in global functioning (primary outcome) at 24 weeks (primary endpoint) after the MRB intervention compared to the children whose parents had attended the LAA group. There are a number of secondary outcomes (measured at the end of the intervention and at 24-week follow-up), these include whether (i) parents increase their knowledge and skills in understanding and managing their child’s challenging RRB; (ii) children show a reduction in challenging RRB, and change in participation in everyday activities, parent stress and impact on family life; (iii) the intervention provides value for money for the NHS; and (iv) these improvements are maintained at 1 year from baseline.

We have carefully selected end of group and follow-up (24 and 52 weeks) outcome measures to capture both independent (blinded researcher), teacher and parent-reported changes. These include blinded ratings of improvement in child’s overall functioning (assessed using Clinical Global Impressions–Improvement (CGI-I)) and change in challenging RRB. Parent questionnaires will also provide information on child RRB, child participation and daily living skills, parent stress, self-efficacy and impact on family life. Parents will be aware of group status but teachers and the primary outcome assessor will be blind to group allocation.

We will evaluate maintenance of effect at the 52-week follow-up appointment which will also allow us to investigate any potential longer-term (downstream) impact on child and family functioning (e.g. social participation).

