### Participant timeline

#### Procedures

##### Data collection

Baseline assessment and follow-up measures will be collected by RAs blinded to the outcome of randomisation. RAs are trained to high levels of reliability in all baseline characterisation and outcome measures (see Table 1). All families will be allocated a unique number that will be used to identify them on all paper assessment forms throughout the trial. All data collected on paper will be inputted into a data management system for statistical analysis and all identifying data will be stored securely separately. The Clinical Data Management System (Elsevier’s MACRO) used for this trial is fully compliant with all regulatory frameworks for research of this nature. Patients cannot be identified from eCRFs. The CI or delegated person will monitor completeness and quality of data recording in eCRFs and will correspond regularly with site PIs (or their delegated team member) with the aim of capturing any missing data where possible and ensuring continuous high quality of data. All study data will be treated in accordance with the latest Directive on Good Clinical Practice (2005/28/EC).

**Table 1 Tab1:** Time points at which measures and data are collected

Procedure	Screening	Baseline	Treatment phase	Follow-up		
			Weeks 1–8	Week 10	Week 24	Week 52
Informed consent	X					
Child and parent demographics*	X				X	X
Eligibility	X					
ADOS-2		X				
SRS-2		X				
CGI-I					X	
RBQ-2		X		X	X	X
Teacher RBQ-2		X		X	X	X
Measurement of the target behaviour vignette		X		X	X	X
VABS 3		X			X	
Parent self-efficacy questionnaire		X		X	X	X
Autism Parenting Stress Index		X		X	X	X
WEMWBS		X			X	X
Autism Family Experience Questionnaire		X			X	X
Proxy completed CHU9D		X			X	X
EQ-5D-5L		X			X	X
Resource use questionnaire		X			X	X
Time and travel questionnaire		X				
Randomisation**		X				
Weekly intervention (MRB or Learning About Autism)			X			

*Child demographics to include child age, gender, type of nursery/school, diagnosis, current medications, additional diagnoses, ethnicity and previous intervention exposure

*Parent demographics to include level of education, employment status, family structure, attendance at previous courses or interventions relating to children with a diagnosis of ASD

**Randomisation to take place following completion of baseline assessment

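### The difference-in-difference model for continuous secondary outcomes is less precise than baseline adjustment, could miss parent-group clustering depending on an unstated group term, and leaves out week 10

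*Protocol article*

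**What the plan says.** The Analysis plan section of the protocol article sets the method for continuous secondary outcomes: "The continuous secondary outcomes will first be analysed at 24 weeks using a difference-in-difference model based on linear mixed effect model", with the model "accounting for paired data (at baseline and at 24 weeks) per child and clustering of children by parent groups". For the later follow-up it adds: "The same model will be applied to the data at week 52, which will be analysed as longitudinal data incorporating data at baseline and 24" (the last figure being the 24-week visit). It does not say whether the parent-group term is constant over time or differs between baseline and follow-up.

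Three other places bear on this:

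- A footnote to Table 1 fixes the order of events: "Randomisation to take place following completion of baseline assessment".
- The Study aims section describes the evaluation as "compared with a parent autism psychoeducation group, at 10, 24 and 52 weeks follow-up". Table 1 marks RBQ-2, teacher RBQ-2, the target behaviour vignette, parent self-efficacy and the Autism Parenting Stress Index (APSI) at week 10.
- The Methods paragraph of the abstract, having described the GEE for the primary outcome, says: "All secondary outcomes will be analysed in a similar way using appropriate distribution and link function".

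**The concern.** Difference-in-difference is useful when groups may differ at the start. Here baseline precedes allocation, so the arms have equal baseline means in expectation. Estimating those means freely gives away precision that baseline adjustment would keep.

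The order of events also matters for clustering. Correlation produced by sitting in the same parent group can exist only after baseline. A group term that takes the same value at baseline and follow-up cannot represent it, and that term drops out of the arm-by-time contrast. If the model were fitted that way, standard errors would be too small for the continuous secondary outcomes, such as repetitive behaviour, parenting stress and self-efficacy.

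Finally, the aim includes a comparison at 10 weeks, but the data named for the two models are baseline, week 24 and week 52. As written, no model for continuous outcomes answers the 10-week question.

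**Working it through.** **Inputs.** From the Sample size section: 224 evaluable families, an average of 8 per parent group, ICC 0.10. This gives 224/8 = 28 groups, 14 per arm. The ICC is a planning value for the binary primary outcome, and the article gives none for the continuous outcomes. It also gives no baseline to follow-up correlation. I therefore assume ρ from 0.3 to 0.8 and ICC from 0.01 to 0.10, no clustering at baseline, and follow-up SD 1. The plan states no figure for this model, so there is none to reproduce.

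**Precision without clustering.** The change score has variance proportional to 2(1−ρ). The baseline-adjusted estimator has variance proportional to 1−ρ². The ratio is 2/(1+ρ): 1.54 at ρ = 0.3, 1.33 at 0.5, 1.18 at 0.7 and 1.11 at 0.8.

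**Precision with clustering modelled correctly.** Take ρ as the child-level correlation, with child-level variance 1−ICC and a group effect of variance ICC at follow-up only. With m = 8:

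- change score: V_c = 2(1−ρ)(1−ICC) + 8·ICC
- baseline-adjusted: V_a = (1−ρ²)(1−ICC) + 8·ICC

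| ρ (ICC 0.10) | V_c | V_a | V_c/V_a |
|---|---|---|---|
| 0.3 | 2.06 | 1.619 | 1.27 |
| 0.5 | 1.70 | 1.475 | 1.15 |
| 0.7 | 1.34 | 1.259 | 1.06 |
| 0.8 | 1.16 | 1.124 | 1.03 |

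If ρ is instead defined on the total scale with equal variance at both times, the ratio is [2(1−ρ)+0.7]/[1−ρ²+0.7], which is 1.17, 1.12 and 1.07 at ρ = 0.5, 0.6 and 0.7. At ρ = 0.5, a comparison with 90% power under baseline adjustment would have about 80% power without clustering and about 85% with it.

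**If the group term is a time-constant intercept.** The model then reports the standard error of an unclustered change-score comparison, √(4·s²/224), where s² = 2(1−ρ)(1−ICC) + ICC. At ρ = 0.5 and ICC 0.10, s² = 0.9 + 0.1 = 1.0. The reported standard error is √(4/224) ≈ 0.13, while the true one is √(4×1.70/224) ≈ 0.174. Mixed-model fits to simulated data confirmed the cancellation: in one data set the standard error was 0.1213 both from the model and from the formula ignoring groups. Adding a group-by-time effect gave 0.155 to 0.182 over three data sets.

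The variance is understated by the factor D = V_c/s², so type I error is about 2[1−Φ(1.96/√D)].

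| ICC | ρ | D | Closed form | Simulated (4,000 runs) |
|---|---|---|---|---|
| 0.01 | 0.5 | 1.07 | 5.8% | not run |
| 0.05 | 0.5 | 1.35 | 9.2% | 9.6% |
| 0.05 | 0.7 | 1.57 | 11.7% | 12.0% |
| 0.10 | 0.5 | 1.70 | 13.3% | 12.3% |
| 0.10 | 0.7 | 2.09 | 17.6% | 17.7% |

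Analysing group means of change on the same simulated data held 4.8–5.2%. A separate simulation at ICC 0.10 with 8,000 runs per setting gave 13.6%, 15.3% and 18.5% at ρ = 0.5, 0.6 and 0.7.

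**Week 10 and the abstract.** The 24-week model uses the baseline and 24-week pair, and the week-52 analysis adds "which will be analysed as longitudinal data incorporating data at baseline and 24 weeks". Week 10 is a planned assessment and appears in the aim, but in neither model. The abstract describes the secondary analyses as similar to the GEE. The Analysis plan keeps GEE for binary or categorical outcomes and uses a mixed model for continuous ones.

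**The case against.** A reader might infer that the plan's model certainly ignores parent-group clustering and that its secondary outcomes will carry inflated false-positive rates. The article does not support that. It says clustering is accounted for and names no random-effects structure. A group-by-time term fits the wording equally well and removes the problem. Such detail is ordinary content for the statistical analysis plan, which the article says will be agreed before any analysis. The inflation also depends on an ICC borrowed from the binary primary outcome and on no clustering at baseline. Stable correlation between families in the same area would properly cancel in a change contrast. This objection stands: the clustering point is a conditional risk.

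It can also be said that difference-in-difference is unbiased under randomisation and that the precision loss is small once clustering is modelled. Both are true. The estimator itself, however, is stated in the article, and the better one needs no extra data.

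On week 10, the article does not rule out an analysis, and VABS 3, WEMWBS and the Autism Family Experience Questionnaire have no week-10 visit. With complete week-24 data, week 10 adds little to the 24-week contrast. Its value lies in the 10-week comparison itself and in handling missing data. The mismatch with the stated aim remains.

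**Conclusion.** The point holds for the continuous secondary outcomes only. The stated estimator is valid but avoidably imprecise: 1.03 to 1.27 times the variance of baseline adjustment at ICC 0.10 with groups of 8 and ρ from 0.8 to 0.3, and 1.33 times without clustering at ρ = 0.5. The risk to type I error arises only with a time-constant group intercept and no baseline clustering. Under those conditions it runs from about 6% at ICC 0.01 (ρ = 0.5) through 9–12% at 0.05 to 12–18% at 0.10 (ρ = 0.5 to 0.7). All values of ρ, and the ICCs for these outcomes, are assumptions.

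The omission of week 10 from the stated models and the conflict between abstract and Analysis plan are real but lesser points. The primary GEE and the sample size are not affected.

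**What to change.** For each continuous secondary outcome, specify one baseline-adjusted (or constrained-baseline) linear mixed model with:

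- post-baseline outcomes at weeks 10, 24 and 52, wherever the measure is collected;
- fixed effects for baseline value (or a common baseline mean), arm, visit, arm-by-visit and the minimisation factors;
- a child-level covariance across visits;
- a parent-group effect acting on post-baseline visits only;
- small-sample degrees of freedom, such as Kenward–Roger, given about 28 groups.

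Report the treatment contrast at each measured visit, so that the 10-week aim has an analysis. If the difference-in-difference form is kept, state explicitly that the group effect may differ between baseline and follow-up. Align the abstract's sentence on secondary outcomes with the Analysis plan.

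The cost is wording in the statistical analysis plan and the abstract. No new data are needed, and correctly specified baseline adjustment loses no precision against a correctly clustered change score.

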### Health economics

#### Economic evaluation

The economic evaluation will be carried out from the perspective of the NHS and personal social services. A cost-effectiveness analysis within trial which will compare the costs to achieve the target mean difference in the CGI-I in both the MRB and Learning About Autism groups at 24 weeks. A cost-utility approach will also be undertaken using the data from the CHU9D questionnaire to synthesise QALYs for the children and compare the interventions using an incremental costs per QALY approach. To measure the benefits which would not be captured in the metric of a QALY. Finally, a cost-consequence will be used to compare costs and benefits from a wider perspective (for example the broader costs to families).

#### Measurement of effects

For the cost-effectiveness analysis, the effectiveness measure will be based on the results from the primary trial outcome; the target mean difference in the CGI-I.

The costs utility analysis will use the responses from the CHU9D based on the proxy responses from child’s caregiver. The CHU9D will be administered at baseline, 24 weeks and 52 weeks. This will measure the quality of life of the child which will be converted into QALYs for each child using the under the curve approach and an average incremental cost per QALY in each randomised arm will be calculated.

The caregiver will complete ED-5D-5L at baseline, 24 and 52 weeks. These responses will measure quality of life in relation to the caregiver and will be scored using the values sets for England. This data will also be converted into QALYs using the under the curve approach. The QALYs which are calculated for the carers will be included as part of the cost-consequence analysis. Further consequences will be examined as part of the cost consequences analysis including primary and secondary clinical outcomes, particularly the health-related quality of life of the child and their care-giver. These will include benefits which cannot be included with the scope of the QALY outcome.

#### Analysis

For the cost-effectiveness analysis, an incremental cost per unit change in the CGI-I scale will be calculated, with the aim of calculating the cost for achieving a minimally important difference in the CGI-I. Point estimates of costs and effects, cost effect plots and acceptability curves will be produced. Statistical imprecision and uncertainty will be examined using a stochastic sensitivity analysis. The cost-utility analysis will be analysed in a similar way, to the cost-effectiveness analysis. A formal decision analytic model is not currently planned but may be used if the cost of the intervention is not offset by a reduction in resource use or gain in QALYs for the child. If the results are conclusive (i.e. the intervention more effective and less costly or less effective and more costly) then a model will not be required.

The cost-consequence analysis will present the costs and consequences as a difference between randomised groups with appropriate measures of variance.

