#### Economic outcome measures

##### Primary economic outcome measure

Incremental costs to achieve target difference in the CGI-I at 24 weeks: The improvement scores from the CGI-I will be taken from each randomised arm of the trial to inform the efficiency of the intervention. A cost per incremental improvement of CGI-I scale will be calculated in each pathway.

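### The primary cost-effectiveness ratio is stated with three different effect measures, one of them misdescribing the binary primary outcome as a mean difference, and incremental ratios are described arm by arm

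*Protocol article*

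**What the plan says.** The article gives the effect measure of the within-trial cost-effectiveness analysis in several places.

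- **Additional improved child.** Abstract, Methods: "incremental cost per additional child achieving at least the target improvement in CGI-I scale at 24 weeks".
- **Target difference or target mean difference.** Primary economic outcome measure: "Incremental costs to achieve target difference in the CGI-I at 24 weeks". Economic evaluation will "compare the costs to achieve the target mean difference in the CGI-I in both the MRB and Learning About Autism groups at 24 weeks". Measurement of effects: "the effectiveness measure will be based on the results from the primary trial outcome; the target mean difference in the CGI-I".
- **Scale points.** Health economics, Analysis: "an incremental cost per unit change in the CGI-I scale will be calculated", with the stated purpose of costing a minimally important difference. Primary economic outcome measure has similar wording: "A cost per incremental improvement of CGI-I scale will be calculated in each pathway".

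The clinical primary outcome is binary. The Abstract compares the proportion of children improved, Analysis plan specifies a GEE with binomial distribution and logit link, and Sample size is built on a 20% difference in improvement rate.

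On arms, Primary economic outcome measure speaks of each pathway, Secondary economic outcome measures of an incremental cost per QALY ratio in each arm, and Measurement of effects says that "an average incremental cost per QALY in each randomised arm will be calculated". Economic evaluation, by contrast, says that the two interventions will be compared on incremental cost per QALY.

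**The concern.** A cost-effectiveness ratio takes its meaning from its denominator. An additional improved child, a point on the CGI-I and a minimally important difference are three denominators, and a reader cannot tell which one the trial will report as its primary economic result. The Primary economic outcome measure section, which should settle this, itself mixes the second and third forms.

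Two consequences follow. First, the economic result could be built on an effect other than the one the clinical analysis estimates, because Measurement of effects ties it to a mean difference that is not the primary outcome. Second, several published definitions leave room to choose among them after the data are seen. The Analysis section also promises acceptability curves, whose willingness-to-pay axis needs one effect unit. It drops the decision model when one arm is both more effective and less costly, without saying on which measure effectiveness is judged.

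The per-arm wording adds a further problem. Cost divided by effect within one arm is an average ratio and does not give the value of choosing MRB over LAA.

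**Working it through.** The article states no figure for the economic outcome, so there is none to reproduce. Its only numeric target on the CGI-I is the 20% difference in improvement rate in Sample size. The check is whether each form can be calculated and whether the forms agree.

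**Inputs from the article.** The CGI-I is a 7-point rating of change relative to the child's baseline state (Primary child outcome measure), collected at week 24 only (Table 1).

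**Assumed inputs.** Extra mean cost of MRB, ΔC = £200 per family. Scores run 1 to 7 with lower better (the article gives neither the labels nor the direction). Three sets of between-arm differences are invented for illustration.

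**Formulas.**
- Per additional improved child: ΔC / Δp, where Δp is the difference in proportion improved.
- Per point: ΔC / Δm, where Δm is the difference in mean 24-week score.
- Per minimally important difference of size d, by linear scaling: d × ΔC / Δm.

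For a 1-to-7 score, Δm equals the sum of the six differences in the proportion scoring at or below 1, 2, …, 6. A responder difference is only one of those six terms, so Δm and Δp need not move together.

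**Results.**

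| Case | Δm | Δp, cut at 2 | Δp, cut at 3 | Per point | Per improved child, cut at 2 | Per improved child, cut at 3 |
|---|---|---|---|---|---|---|
| A | 0.51 | 0.20 | 0.20 | 200/0.51 = £392 | 200/0.20 = £1,000 | £1,000 |
| B | 0.33 | 0 | 0.20 | 200/0.33 = £606 | no finite ratio | £1,000 |
| C | 0.50 | 0.20 | 0.10 | 200/0.50 = £400 | £1,000 | 200/0.10 = £2,000 |

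In case A, the cost of a minimally important difference is 0.5 × 392 = £196 if d is half a point and £392 if d is one point. Without a value for d, or for a target mean difference, that form has no fixed result.

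Case B shows more than a change of unit. On mean score MRB is more effective; on the proportion at or below 2 the arms do not differ.

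**Per-arm wording.** Take 40% against 20% improved (assumed) and a mean LAA cost of c. The incremental ratio is 200/(0.40 − 0.20) = £1,000 whatever c is. The within-arm averages are (c + 200)/0.40 for MRB and c/0.20 for LAA. MRB's is lower when c + 200 < 2c, that is, when c > £200, and higher when c < £200. The average ratios therefore turn on the level of cost in LAA, which has no bearing on the incremental ratio.

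**The case against.** The strongest reply is that this is loose drafting in a condensed article. The Abstract's ratio fits the binary primary outcome, and the target difference under Primary economic outcome measure can be read with the 20% in Sample size, leaving the word mean in two sections as the slip. A value for a minimally important difference, or the cut-off for improvement, may sit in the full protocol or a health economics plan. Much of this stands, and the absence of those details is not the complaint. What remains is that the published statements conflict with one another; an unseen plan could choose between them but would not make them agree.

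Three stronger readings are tempting, and the article does not support them.

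- A reader might infer that a ratio per unit change cannot be formed because Table 1 has no baseline CGI-I. The scale is itself a rating of change from baseline, so the between-arm difference in mean week-24 score is enough.
- A reader might infer that the headline ratio is undefined. The Abstract's version matches the primary analysis and can be calculated once the improvement cut-off is set.
- A reader might infer that the trial will judge value on average ratios within arms and so could favour the wrong option. Economic evaluation compares the interventions, and Analysis plans cost-effect plots and acceptability curves and speaks of an arm being more effective and less costly. These are between-arm quantities. The per-arm phrases are faulty wording, not evidence of a different analysis.

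It is also fair that different units give different numbers by definition, and that no threshold is stated for any CGI-I ratio. Case B is the part of the illustration that goes beyond units.

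**Conclusion.** The point holds as an inconsistency in stated rules. The primary economic effect measure appears in three non-equivalent forms, Measurement of effects contradicts the binary primary outcome, and incremental ratios are wrongly described as arm-specific. The article fixes no value for a mean-difference target or a minimally important difference.

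The size cannot be taken from the article. Under the assumed £200 and invented score distributions, the same data give £392 or £1,000 in case A, and a finite or no finite ratio in case B. These figures show only that the choice of measure can alter the conclusion; they do not predict the trial's result. The clinical primary analysis is unaffected. The matter should be corrected because cost-effectiveness is one of the trial's two stated aims and the measure should be settled before data are seen.

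**What to change.** 1. Name one primary ratio throughout: the between-arm difference in mean cost (MRB minus LAA) divided by the between-arm difference in the proportion improved at 24 weeks, using the same CGI-I definition of improvement as the primary analysis.
2. Correct Economic evaluation and Measurement of effects so that they no longer treat the primary outcome as a mean difference, and align Primary economic outcome measure with the same ratio.
3. If a ratio per CGI-I point is wanted, keep it in Analysis as a labelled secondary analysis. Any cost per minimally important difference should sit there too, with its value and source stated in advance.
4. In Primary economic outcome measure, Secondary economic outcome measures and Measurement of effects, replace the per-arm or per-pathway wording with a comparison between arms, for this ratio and for cost per QALY.

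The cost is rewording these sections and the matching text of the health economics plan. No new data, visits or design changes are needed.
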